### Intervention

RIPerC will consist of automatically delivered five cycles of electronic tourniquet inflation to the upper non-paretic limb, each lasting 5 min and separated by 5 min of cuff deflation. The cuff will be inflated to 200 mmHg and it will be applied to the opposite arm to the one experiencing motor and/or sensory deficit in order to reduce the risk of phlebitis and to maintain the somatosensory stimuli. RIPerC will be initiated by the ambulance staff during transportation and it will be finished for all patients in the ambulance or during Hospital admission. All patients in both groups will be treated according to conventional care procedures following international guidelines. Thus, mechanical thrombectomy and intravenous fibrinolysis will be allowed. Revascularization therapies will not be delayed due to the study. The non-interventionist group will use a sham device. It will simulate vibration of the device but no inflation will be performed. Discomfort and complications related to RIPerC will be recorded.

### Primary Outcome

The primary outcome will be the difference in the proportion of patients with good outcomes as defined by a mRS score of 2 or less at 90 days.

### Secondary Outcomes

The secondary outcomes will be: (1) a decrease in the National Institutes of Health Stroke Scale (NIHSS) score greater or equal than 4 between baseline and day one, 5 ± 1 days and 90 ± 7 days; (2) a mRS score of 2 or less at 5 ± 1 days; (3) the rate of serious adverse events related to the intervention; (4) the rate of symptomatic intracerebral hemorrhage (SICH) defined by the Safe Implementation of Thrombolysis in Stroke Monitoring Study protocol at 24–36 hours (15); (5) acute infarct volume; (6) metabolomic and lipidomic response to RIC; and, (7) neuropsychological evaluation of cognitive and affective domains.

In all eligible patients, a brain MRI will be performed within 3–4 days of the onset of symptoms, including the following sequences: (1) transverse T2-FLAIR; (2) transverse T2^*^-weighted gradient-echo; (3) transverse diffusion-weighted (DWI) single-shot echo-planar spin-echo; and, (4) axial 3D time-of-flight MR angiography (through the circle of Willis). All participating centers will follow the same protocol. A neuroradiologist blinded to clinical features and intervention will review the MRI images. Infarct volume will be defined as the hyperintense area on the initial isotropic DWI acquired with a b value of 1,000 sec/mm2.

In addition, we will use metabolomic and lipidomic analyses to define a panel of serum biomarkers accurately related to RIC phenomenon. For these purposes, in 100 patients (50 sham and 50 RIPerC), blood samples for further determination of metabolomics and lipidomics will be drawn at arrival to hospital, at days 3 and 5 as previously performed (16, 17). As we did not have preliminary data and no metabolites have yet been defined we will performed a non-targeted metabolomics and lipidomic profiling in order to identify differential molecules found in the intervention group.

The neuropsychological evaluation will include Montreal cognitive assessment, trail making test part a and b, the Wechsler adult intelligence scale, the free and cued selective reminding test, the apathy evaluation scale and the Rey complex figure test. We also performed the Health-related quality of life assessment questionnaire (EQ-5D) at 90 days.

### Data Monitoring Body

An independent data safety monitoring board (DSMB) will look after the safety of the study. It will ensure that the rate of SICH and serious adverse events is similar in the two groups. An interim analysis will be performed after the inclusion of the first 100 patients for early stopping due to safety reasons. Moreover, the DSMB could recommend stopping the study for safety reasons at any moment and make recommendations to the Executive Committee regarding efficacy, quality and feasibility of the study.

### Sample Size Estimates

A sample size of 280 subjects in each arm achieves 80% power to detect treatment differences of 14% between the intervention and the control groups, using a two-sided binomial test at significance level of 0.05, assuming that 40% of the control patients will experience good outcome defined by a mRS score of 2 or less at 90 days, and allowing a misdiagnosis rate of 29% (15% of haemorrhagic strokes and 14% of mimic stroke conditions). Two extra interim analyses will be performed at 33 and 67% of recruitment on the primary outcome. Early stopping is planned if large differences between the study groups are observed in order to reduce study participants' exposure to the inferior study arm and saving time and resources. Since repeated significance testing on accumulating data will be performed, adjustment of the usual hypothesis testing procedure to maintain the overall significance level of 0.05 will be done by using the flexible type I error spending function (18, 19). Due to the interim analyses, the sample size must be increased by an inflation factor of 1.02, resulting in 572 patients (286 per group).

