## Abstract

**Rationale:** Remote ischemic perconditioning during cerebral ischemia (RIPerC) refers to the application of brief episodes of transient limb ischemia commonly to a limb, it represents a new safe, simple and low-cost paradigm in neuroprotection.

**Aim and/or Hypothesis:** To evaluate the effects of RIPerC on acute ischemic stroke (AIS) patients, applied in the ambulance, to improve functional outcomes compared with standard of care.

**Sample Size Estimates:** A sample size of 286 patients in each arm achieves 80% power to detect treatment differences of 14% in the outcome, using a two-sided binomial test at significance level of 0.05, assuming that 40% of the control patients will experience good outcome and an initial misdiagnosis rate of 29%.

**Methods and Design:** We aim to conduct a multicentre study of pre-hospital RIPerC application in AIS patients. A total of 572 adult patients diagnosed of suspected clinical stroke within 8 h of symptom onset and clinical deficit >0 according to prehospital rapid arterial occlusion evaluation (RACE) scale score will be randomized, in blocks of size 4, to RIPerC or sham. Patients will be stratified by RACE score scale. RIPerC will be started in the ambulance before hospital admission and continued in the hospital if necessary. It will consist of five cycles of electronic tourniquet inflation and deflation (5 min each). The cuff pressure for RIPerC will be 200 mmHg during inflation. Sham will only simulate vibration of the device.

**Study Outcome(s):** The primary outcome will be the difference in the proportion of patients with good outcomes as defined by a mRS score of 2 or less at 90 days. Secondary outcomes to be monitored will include early neurological improvement rate, treatment related serious adverse event rates, size of the infarct volume, symptomatic intracranial hemorrhage, metabolomic and lipidomic response to RIPerC and Neuropsychological evaluation at 90 days.

**Discussion:** Neuroprotective therapies could not only increase the benefits of available reperfusion therapies among AIS patients but also provide an option for patients who are not candidates for these treatments. REMOTE-CAT will investigate the clinical benefit of RIC as a new neuroprotective strategy in AIS.

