### Statistical Analyses

Included patients will be described with respect to demographic and clinical characteristics, according to the study arm. Continuous variables will be summarized using means and standard deviations for normally distributed data; or median and 25–75% percentiles for non-normally distributed data. Normal distribution will be assessed by means of the Shapiro–Wilks test, rejecting normality when *p* <0.05. Categorical data will be summarized using counts and percentages. Comparisons will be performed by means of the Pearson's chi-squared test for categorical variables; the *t*-test for normally distributed data; and the Mann–Whitney *U*-test for non-normally distributed data.

Primary analysis will be performed by means of the binomial test. If the study groups are unbalanced, the primary outcome will be compared using a logistic regression model that will include the variables exhibiting baseline differences as covariates.

Secondary outcomes will be compared using the most appropriate test according to the distribution of the data. As with the primary analysis, secondary outcomes and safety outcome analyses will be conducted using multivariable generalized linear models with suitable links.

The analysis will be performed on the intention-to-treat set and will be repeated on the per-protocol set as a sensitivity analysis.

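### The sample size gives 80% power only for confirmed ischaemic stroke, but the main analysis is intention-to-treat, where power is about 66 to 73% if misdiagnosed patients do not respond

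*Protocol article*

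**What the plan says.** The Sample Size Estimates section starts from "A sample size of 280 subjects in each arm". The target is 80% power for a 14-point gap in good outcome over a control rate of 40%, tested two-sided at the 5% level. The number already includes an allowance for wrong field diagnoses, described there as "allowing a misdiagnosis rate of 29% (15% of haemorrhagic strokes and 14% of mimic stroke conditions"). A further allowance covers the interim looks: "Due to the interim analyses, the sample size must be increased by an inflation factor of 1.02, resulting in 572 patients (286 per group"). The Abstract repeats the claim for the final number: "A sample size of 286 patients in each arm achieves 80% power to detect treatment differences of 14% in the outcome".

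The Statistical Analyses section names the analysis population: "The analysis will be performed on the intention-to-treat set and will be repeated on the per-protocol set as a sensitivity analysis".

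Three other places bear on who is in that population. Under Randomization, and in the procedures table, patients are allocated in the ambulance. The Discussion acknowledges that the definitive diagnosis comes only at hospital. The footnote to the procedures table keeps haemorrhage patients to the 90-day visit, but follows patients without brain ischaemia only to discharge and then through registries. The article nowhere defines a primary set restricted to confirmed ischaemic stroke.

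**The concern.** Dividing a sample size by 0.71 is right when 29% of patients contribute nothing to the analysis: the patients who remain carry the full effect, and enough of them are left. It is not right when the 29% stay in. They then add to the denominator but, if the treatment does nothing for them, not to the difference. The expected effect shrinks, and replacing patients one for one does not make up for that.

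By the article's own description, haemorrhages and mimics are randomised patients. On the plain meaning of intention-to-treat they belong to the main analysis. The 80% would then describe a population that is not the one tested. A neutral result could reflect dilution rather than absence of benefit in ischaemic stroke, and the two efficacy looks at 33% and 67% of recruitment would be diluted in the same way.

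**Working it through.** **Inputs (Sample Size Estimates):** control rate 0.40, intervention rate 0.54, two-sided alpha 0.05, power 80%, misdiagnosis 29% (15% haemorrhage, 14% mimics), interim factor 1.02, equal arms. **Assumption, not in the article:** no treatment effect in haemorrhages or mimics. Their good-outcome rates are not given either, so they are varied.

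**1. Reproducing the plan's figure.** Two-proportion formula with pooled variance under the null:

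n = [z(α/2)·√(2p̄(1−p̄)) + z(β)·√(p₁(1−p₁)+p₂(1−p₂))]² / Δ²

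With p̄ = 0.47 and Δ = 0.14:
- 1.960 × √(2 × 0.47 × 0.53) = 1.3834
- 0.8416 × √(0.24 + 0.2484) = 0.5882
- n = (1.3834 + 0.5882)² / 0.0196 = 3.887 / 0.0196 = 198.3 per arm
- 198.3 / 0.71 = 279.3, so 280
- 280 × 1.02 = 285.6, so 286

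The arcsine formula also gives 280 (198.2 / 0.71 = 279.1). Other routes miss: unpooled variance gives 195.6 / 0.71 = 275.5, a continuity correction gives 213 / 0.71 = 300, and multiplying by 1.29 instead of dividing by 0.71 gives about 257. The 29% has therefore been treated as lost to the analysis.

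**2. Power in confirmed ischaemic stroke.** 280 × 0.71 = 199 per arm, 40% versus 54%: 80.1%. At 286 the count is 286 × 0.71 = 203 per arm. With three looks and an O'Brien-Fleming-type spending function (my assumption; critical values 3.73, 2.50, 1.99) power is 80 to 81%.

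**3. Power on all randomised patients, no effect in the 29%.**
- Expected difference: 0.71 × 14 = 9.94 points
- At 280 per arm, 40% versus 49.94%: (0.0994 × √280 − 1.3789) / 0.7000 = 0.406, which is a power of 65.8%
- At 286 in a fixed design: 66.7%. The extra 2% pays for the interim looks; with the three looks above, power is about 66%.

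The good-outcome rate in misdiagnosed patients matters little: power is 65.3 to 67.4% at 280 per arm for rates from 20% to 80%, and at most about 70% at the extremes of 0% or 100%.

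**4. Mimics without a 90-day mRS drop out, haemorrhages stay.**
- Per arm: 280 × 0.86 = 241
- Difference: 9.94 / 0.86 = 11.6 points
- Power: 72.2 to 73.5% for good-outcome rates in haemorrhage from 40% down to 10%

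**5. What would give 80% on all randomised patients.**
- Detectable overall difference: about 11.7 to 11.8 points, that is, about 16.5 to 16.6 points in ischaemic stroke (divide by 0.71) if nobody else responds.
- Alternatively, keeping 14 points in ischaemic stroke, some benefit among the misdiagnosed. With an overall control rate of 40% at 280 per arm, 11.77 points are needed and 11.77 / 14 = 0.841. If only haemorrhages respond, they need (0.841 − 0.71) / 0.15 = 87% of the ischaemic effect. If haemorrhages and mimics respond alike, they need (0.841 − 0.71) / 0.29 = 45%.
- Alternatively, more patients: 392 per arm for 9.94 points, × 1.02 = about 400 per arm.

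**6. Cross-check.** If all 280 per arm carried the full 14 points, power would be 91.5%, and no misdiagnosis allowance would have been needed.

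**The case against.** The strongest reply is that this is a condensed article. It does not define the intention-to-treat set, and the full protocol or analysis plan may restrict it to confirmed ischaemic stroke. The aim is worded for ischaemic stroke patients, the sample size is inflated for misdiagnosis, and mimics are followed less closely; all of this points that way. If so, the 80% stands and only the wording of the analysis section is at fault. That is fair, and it is why the point is a mismatch between two statements rather than a missing definition. As published, the two statements do not fit together: patients are randomised before diagnosis, and nothing in the article narrows the set.

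A second reply is that 66% is one scenario. That also stands. It needs mimics in the analysis, either with a 90-day mRS from registries or through the multiple imputation under Handling Missing Data, and no effect in any misdiagnosed patient. A complete-case analysis without mimics gives about 72 to 73%. Both are below 80%.

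Four stronger readings are tempting and not supported:
- That the sample size arithmetic is wrong. It reproduces.
- That intention-to-treat could reach 80% only if haemorrhages benefited as much as ischaemic strokes. Step 5 shows that somewhat less in haemorrhages, or about half the effect in all misdiagnosed patients, would do. The article gives no grounds to expect either, and itself counts these patients as misdiagnosed.
- That the primary set ought to be confirmed ischaemic stroke. For a treatment started before diagnosis, the effect in all treated patients is an equally defensible question.
- That the trial's estimate or type I error is compromised. Loss of power does neither.

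**Conclusion.** The concern holds as a mismatch between the population used for the sample size and the population named for the main analysis. For 286 per arm, power is about 80% in confirmed ischaemic stroke. Under intention-to-treat it is about 66% with all randomised patients analysed, or about 72 to 73% if mimics fall out. On the first of these the type II risk is about 34% instead of the stated 20%.

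These figures rest on the article's own 40%, 14 points and 29%, on misdiagnosis being equally common in both arms, and on no effect in haemorrhages and mimics. The last is an assumption. It agrees with the way the sample size was built but is not stated in the article; 80% under intention-to-treat would require substantial benefit in misdiagnosed patients. Because the point concerns the headline power of the primary analysis, the text should be corrected.

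**What to change.** Make the two sections agree. The minimum is to restate the Sample Size Estimates section and the Abstract along these lines: 286 per arm gives about 80% power to detect 40% versus 54% in patients with confirmed ischaemic stroke; under intention-to-treat, assuming no effect in haemorrhages and mimics, power is about 66 to 73% depending on whether mimics have a 90-day mRS, and with all randomised patients analysed the overall difference detectable with 80% power is about 11.7 to 11.8 points. The no-effect assumption should be written out.

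If the sponsor instead means confirmed ischaemic stroke to be the primary set, the Statistical Analyses section must say so, with the diagnosis adjudicated blind to arm and the full intention-to-treat result reported alongside. That choice of question is the sponsor's.

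Both routes cost wording only; the first makes the published power less favourable. A third route, keeping full intention-to-treat and 80% power for the diluted 9.9-point difference, would need about 400 per arm, or 800 in total: 228 more than the 572 planned.

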### Statistical Analyses

Included patients will be described with respect to demographic and clinical characteristics, according to the study arm. Continuous variables will be summarized using means and standard deviations for normally distributed data; or median and 25–75% percentiles for non-normally distributed data. Normal distribution will be assessed by means of the Shapiro–Wilks test, rejecting normality when *p* <0.05. Categorical data will be summarized using counts and percentages. Comparisons will be performed by means of the Pearson's chi-squared test for categorical variables; the *t*-test for normally distributed data; and the Mann–Whitney *U*-test for non-normally distributed data.

Primary analysis will be performed by means of the binomial test. If the study groups are unbalanced, the primary outcome will be compared using a logistic regression model that will include the variables exhibiting baseline differences as covariates.

Secondary outcomes will be compared using the most appropriate test according to the distribution of the data. As with the primary analysis, secondary outcomes and safety outcome analyses will be conducted using multivariable generalized linear models with suitable links.

The analysis will be performed on the intention-to-treat set and will be repeated on the per-protocol set as a sensitivity analysis.

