# *Patients treated with intravenous rtPA and/or EVT will undergo neuroimaging at 24 h*.

### Randomization

First, patients will be stratified using the rapid arterial occlusion evaluation (RACE) scale score (14) and then, they will be randomly allocated in blocks of size four, to either receive remote ischemic conditioning (RIPerC group) or sham in the ambulance. An on-call physician not involved in the study will perform the randomization using a computer program located in a web server.

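### Allocation is stratified by RACE score, but the primary test ignores RACE and the covariate rule would normally leave it out, so some efficiency is lost

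*Protocol article*

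**What the plan says.** - **Allocation** (Randomization): "First, patients will be stratified using the rapid arterial occlusion evaluation (RACE) scale score", after which "they will be randomly allocated in blocks of size four". The article gives neither the number of RACE strata nor the cut-offs.
- **Primary test** (Statistical Analyses): "Primary analysis will be performed by means of the binomial test". No stratum or covariate is attached to it.
- **Fallback** (Statistical Analyses): "If the study groups are unbalanced, the primary outcome will be compared using a logistic regression model", a model "that will include the variables exhibiting baseline differences as covariates". RACE is not named.
- **Sample size** (Sample Size Estimates): the calculation rests on the same test, "using a two-sided binomial test at significance level of 0.05". It states that the sample "achieves 80% power to detect treatment differences of 14% between the intervention and the control groups", "assuming that 40% of the control patients will experience good outcome".
- **Stratified Analysis**: RACE is not among the factors listed.
- **Availability**: a RACE score above zero is an inclusion criterion (Table 1), and the scale is scheduled before hospital arrival (Table 2).

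**The concern.** Stratifying on a prognostic factor removes that factor's chance imbalance from the treatment difference, so the true variance of the difference falls. A test that ignores the strata still estimates the larger variance that simple randomisation would give. Its standard error is then too large and its real size falls below the nominal level. The trial takes on stratified allocation without collecting the full gain in precision.

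The conditional logistic model does not repair this. It is triggered by observed imbalance, and imbalance in RACE is what the allocation scheme prevents. The rule tends to admit variables that differ by chance and to omit the one severity score used to allocate patients. It also makes the primary model depend on the data. The comparison could move from the difference in proportions named under Primary Outcome to a covariate-conditional odds ratio, and the covariates could differ between the looks at 33% and 67% of recruitment and the final analysis.

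**Working it through.** **1. Reproduce the plan's figure.** Inputs from Sample Size Estimates: 40% versus 54% (40 + 14), two-sided alpha 0.05, power 80%, misdiagnosis 29%, inflation factor 1.02. The two-proportion formula with pooled variance and mean rate 0.47 is

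n = [1.960·√(2·0.47·0.53) + 0.842·√(0.40·0.60 + 0.54·0.46)]² / 0.14² = 198.3, so 199 per arm.

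199 / 0.71 = 280.3, and 280 × 1.02 = 285.6, so 286 per arm. The stated 280 and 286 reproduce with an ordinary unadjusted two-arm comparison.

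**2. Real size of the unadjusted test.** Let R² be the share of the variance in good outcome explained by RACE stratum. The article gives no such figure, so 5–15% is an assumption. With balance within strata the true variance is (1 − R²) times the one the test uses, hence

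size = 2·[1 − Φ(1.960/√(1 − R²))].

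**3. Power at the planned effect.** Start from the plan's 80%, a standardised effect of 1.960 + 0.842 = 2.802. Stratified allocation shrinks the true variance for both analyses:

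- unadjusted: Φ((2.802 − 1.960)/√(1 − R²))
- RACE-adjusted: Φ(2.802/√(1 − R²) − 1.960)

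| Assumed R² | Size, unadjusted | Power, unadjusted | Power, adjusted | Difference (points) |
|---|---|---|---|---|
| 0 | 5.0% | 80.0% | 80.0% | 0 |
| 0.05 | 4.4% | 80.6% | 82.0% | 1.4 |
| 0.10 | 3.9% | 81.2% | 84.0% | 2.7 |
| 0.15 | 3.4% | 81.9% | 86.0% | 4.0 |

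Starting from 79.5% instead, a base that allows for three looks with O'Brien-Fleming-type spending (an assumption, since the article names no particular function), gives 80.1–81.4% against 81.5–85.5%, a difference of 1.4–4.1 points.

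**4. Simulation check.** 200,000 replicates, single look, two equal RACE strata balanced 1:1, 200 evaluable patients per arm, overall control rate 40%, overall difference 14 points, common odds ratio. The stratum rates are assumptions. R² = 0.25·(difference in rates)²/0.24. CMH is the Cochran-Mantel-Haenszel test.

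| Control rate, severe/mild | R² | Size, unadjusted vs CMH | Power, unadjusted vs CMH |
|---|---|---|---|
| 40/40 | 0 | 4.8% vs 4.8% | 80.6% vs 80.6% |
| 30/50 | 0.04 | 4.4% vs 5.1% | 81.1% vs 81.7% |
| 25/55 | 0.09 | 3.8% vs 5.0% | 81.8% vs 84.3% |
| 20/60 | 0.17 | 3.1% vs 5.0% | 82.8% vs 87.2% |

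The gaps of 0.6, 2.5 and 4.4 points agree with the formula. Under the null the unadjusted standard error is about 2%, 5% and 9% too large in the last three rows.

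**Limit of the check.** Steps 3 and 4 treat the evaluable patients as balanced within RACE strata. Misdiagnosed patients are identified after randomisation, so balance among confirmed strokes is only approximate.

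**The case against.** The strongest reply is that nothing here is invalid. The planned test is the one the trial was sized on, it compares the two proportions named in the primary outcome, and its error is on the safe side. That stands, and it limits the point to efficiency. It does not remove the point, because adjustment costs nothing when RACE is not prognostic (80.6% against 80.6% in the simulation).

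A second reply is that covariate lists belong in the statistical analysis plan, which is not shown. That would hold if the article were silent. It is not: it names the primary test and fixes a rule for choosing covariates, and the rule works against the stratification factor.

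A third reply is that every magnitude depends on an unstated link between RACE and the 90-day mRS. This is correct. The direction is secure, but the size is a range under assumption.

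Some stronger readings are tempting and are not supported:

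- **That the power loss is 2–6 points.** This follows only if the unadjusted test is held at its nominal power while the adjusted test gets the reduced variance. The unadjusted test's own power also rises under stratification, which leaves about 1–4 points.
- **That the binomial test means a one-sample test.** Sample Size Estimates uses the same term for a comparison between two groups, and its figures reproduce from a two-proportion formula.
- **That the size of the gain can be stated for the intention-to-treat set with misdiagnosed patients included.** That needs outcome rates in haemorrhages and mimics, which the article does not give.

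**Conclusion.** The point holds as a loss of efficiency. Allocation is stratified by RACE, the primary test ignores it, and the fallback would normally exclude it. For an assumed R² of 5–15% the unadjusted test runs at about 4.4–3.4% instead of 5% and gives up about 1–4 points of power at the planned effect of 40% versus 54%. The loss is zero if RACE does not predict outcome.

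A reader might infer that the mismatch inflates false positives or by itself pulls the trial below 80% power. Neither follows. The error is conservative, and under the plan's own inputs the unadjusted test still reaches its planned power. The change should be made because it is cheap and also removes a data-dependent choice of primary model, not because the present test would mislead.

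**What to change.** Make three changes to Statistical Analyses.

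1. Prespecify RACE in the primary analysis whatever the observed balance. Use either a Cochran-Mantel-Haenszel risk difference by the RACE strata used at randomisation, or logistic regression with arm and RACE reported as a standardised risk difference with 95% CI. Both keep the difference in proportions as the primary measure.
2. Use that same statistic at the 33% and 67% looks and at the final analysis.
3. Delete the rule that selects covariates from observed baseline differences. If covariates beyond RACE are wanted, name them in advance.

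The cost is wording only. RACE is needed for eligibility and allocation, so it should be complete for every randomised patient, and the sample size can stay as it is. The change should be fixed before any outcome comparison by arm is seen. At the article's status date 76 of 572 patients had been recruited (13%), short of the first look on the primary outcome at 33%.

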**Figure 1 F1:**
[figure not shown]
Graphical representation of REMOTE-CAT clinical trial procedures. After Stroke Code activation in the ambulance, remote ischemic perconditioning (RIPerC) is applied by an automatic device during transportion to the nearest Stroke care center. Usual medical care will be performed in the stroke center.

**Table 2 T2:** Study procedures for eligible patients with AIS.

**Time points**	**Prehospital**	**Admission**	**24 h**	**3 days**	**5 days**	**3 months**
Enrollment						
Eligibility screen	✓					
Patient/family information	✓	✓				
Acute waiver of consent	✓					
Randomization	✓					
RACE scale	✓					
Blood pressure	✓	✓^‡^				
Informed consent		✓				
AIS confirmation		✓^*^			✓^*^	
Demographics and medical history		✓				
Reperfusion therapies		✓				
Intervention						
RIC/Sham application	✓					
Complications related to RIC		✓	✓		✓	✓
Assessment						
NIHSS		✓	✓		✓	✓
Modified Rankin scale		✓			✓	✓
Neuroimaging		✓	✓^#^			
MRI				✓		
Blood biomarkers		✓		✓	✓	
Stroke etiology					✓	
Quality of life						✓
Neuropsychological evaluation						✓
Safety measurement						
Intrahospital complications					✓	✓
SICH			✓		✓	

RACE, rapid arterial occlusion evaluation; AIS, acute ischemic stroke; RIC, remote ischemic conditioning; MRI, magnetic resonance imaging; NIHSS, National Institutes of Health Stroke Scale.

‡ Blood pressure will be reported at the end of RIC/Sham application and 1 h after.

* Patients with intracranial hemorrhage will complete the 90 days follow-up. Patients without evidence of brain ischemia will be followed until discharge and through registries.

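### The primary model and its covariates are chosen from observed baseline imbalance between arms, so the confirmatory analysis and its effect measure are not fixed in advance

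*Protocol article*

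**What the plan says.** The Primary Outcome section defines the effect, measured at 90 days, on the absolute scale: "The primary outcome will be the difference in the proportion of patients with good outcomes as defined by a mRS score of 2 or less". Statistical Analyses then states "Primary analysis will be performed by means of the binomial test". It adds that, should the groups prove unbalanced, the primary outcome is to be analysed with "a logistic regression model that will include the variables exhibiting baseline differences as covariates".

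The article gives no measure or threshold of imbalance, no list of variables to inspect and no named covariate. The only comparison tests the section describes are those introduced by "Comparisons will be performed by means of the Pearson's chi-squared test for categorical variables", with the t-test and the Mann–Whitney test for continuous data. It does not say that these tests are the trigger.

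Under Randomization, "patients will be stratified using the rapid arterial occlusion evaluation (RACE) scale score". RACE is not named as a covariate in any analysis. The same Statistical Analyses section says that secondary and safety outcomes will use multivariable models in the manner of the primary analysis, although the default primary analysis is unadjusted.

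**The concern.** After randomisation, baseline differences between arms are chance. A covariate belongs in the primary model because it predicts the outcome, not because it happens to differ. A rule keyed to imbalance admits irrelevant variables that differ and leaves out strong predictors that balance. The factor used to stratify the randomisation is the one most likely to be left out, because stratification makes it balance.

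The two branches also answer different questions. The binomial branch compares proportions. A logistic model gives by default an odds ratio conditional on whichever covariates entered, and the article describes no conversion back to a difference. Because the trigger is undefined, someone must judge after seeing baseline data by arm whether the groups are unbalanced and on what. That leaves discretion in the trial's single confirmatory result.

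**Working it through.** **1. The plan's own figure.** Inputs from Sample Size Estimates: 40% versus 54%, two-sided 0.05, 80% power, 29% misdiagnosis, inflation factor 1.02. With pooled variance and mean rate 0.47:

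n per arm = [1.960·√(2·0.47·0.53) + 0.842·√(0.40·0.60 + 0.54·0.46)]² / 0.14² = (1.383 + 0.588)² / 0.0196 ≈ 198.3, or 199.

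198.3/0.71 = 279.3, rounded up to 280; 280 × 1.02 = 285.6, rounded up to 286 per arm, 572 in total. The stated size reproduces and rests on the unadjusted test alone.

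**2. How often chance alone triggers the switch.** Assumption, not in the article: unbalanced means p<0.05 on at least one of k independent baseline variables. The probability is 1 − 0.95^k.

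| k | Probability |
|---|---|
| 5 | 23% |
| 10 | 40% |
| 15 | 54% |
| 20 | 64% |

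**3. The effect measure on each branch.** At the design rates the difference is 54 − 40 = 14 points. The unadjusted odds ratio is (0.54/0.46)/(0.40/0.60) = 1.76. A conditional odds ratio further depends on which covariates entered the model.

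**4. Type I error.** Simulations used a single look and no RACE stratification, with the p<0.05 trigger. With 10 or 15 covariates, two of them prognostic (log-odds 1.0 and 0.6 per SD), and 10,000 trials per setting, the conditional rule had size 4.2 to 4.8% at N = 398 and N = 572. With 14 covariates, n = 406 and 3,000 trials, it had 4.3 to 4.9%. The Monte Carlo standard error is √(0.05·0.95/10,000) = 0.2 points and √(0.05·0.95/3,000) = 0.4 points respectively. So size is at or slightly below 5%. Running both analyses and keeping the smaller p-value gave 5.2 to 5.8%; the article does not describe doing that.

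**5. Power.** There were 14 covariates, three of them prognostic. Two settings were used: correctly diagnosed patients only (572 × 0.71 ≈ 406, 40% versus 54%), and all 572 patients with a diluted effect (0.71 × 54% + 0.29 × 40% = 49.9% versus 40%). The second assumes 40% good outcome in both arms among misdiagnosed patients, which the article does not state.

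| Log-odds per SD (assumed) | n = 406: rule / fixed covariates | n = 572: rule / fixed covariates |
|---|---|---|
| 0.9, 0.6, 0.4 | 82% / 89% | 66% / 77% |
| 0.5, 0.3, 0.2 | 81% / 84% | 67% / 70% |
| 0.3, 0.2, 0.1 | 81% / 82% | 66% / 67% |

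Fixed prognostic covariates gain between 1 and 11 points. Against the unadjusted test the conditional rule neither gains nor loses materially: 82.1% versus 82.2% at n = 406 with the strongest set.

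**6. Does the branch change the conclusion?** The unadjusted and conditional analyses disagreed on significance in about 1 to 5% of simulated trials.

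**The case against.** The strongest reply is that no harm to validity is shown. Size stays at or just under 5%, and power matches the unadjusted test for which the trial was sized. The two analyses rarely disagree, and covariate lists are commonly left to a statistical analysis plan. The first three points stand. A reader might infer that the rule inflates type I error or costs planned power; the simulations support neither. The shortfall is against a better analysis that the protocol never claimed. The last point does not remove the concern: the article states a rule, and a later plan could repair it only by replacing that rule.

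It can also be said that the article does not say the binomial result is dropped once the logistic model is run. That is so, but then it does not say which of the two is confirmatory.

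Two further readings are tempting and are not supported:

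- *Re-selection at each look.* Sample Size Estimates says "Two extra interim analyses will be performed at 33 and 67% of recruitment on the primary outcome", so a reader might infer that a different model could be chosen each time. Nothing applies the imbalance rule at the interim analyses, and the effect of doing so has not been quantified.
- *Post-treatment blood pressure as a covariate.* The Table 2 footnote says "Blood pressure will be reported at the end of RIC/Sham application and 1 h after". It marks only the admission reading; a separate prehospital reading exists, and nothing calls the later one baseline.

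Admission NIHSS is a closer case. Table 2 first records NIHSS at admission, after RIC/Sham has begun, and Secondary Outcomes measures change from baseline NIHSS. Even so, the article does not name it as a covariate. It is a reason to restrict the covariate set, not an error already made.

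**Conclusion.** The concern holds as a badly fixed rule for the primary analysis. It should be corrected, but it is not a demonstrated threat to the error rate. As written, an undefined judgement about baseline imbalance decides whether the primary outcome is adjusted, for what, and on which effect scale; RACE enters only by accident.

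The cost is an unfixed confirmatory analysis, room for discretion, and forgone power of roughly 1 to 11 points. That range depends entirely on assumed prognostic strengths. The 23 to 64% trigger frequency depends on an assumed 0.05 threshold and on 5 to 20 independent variables. All simulations ignore the interim looks and the stratification. The planned 572 patients are not in question.

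**What to change.** Delete the imbalance trigger. Pre-specify one primary model and use it at every efficacy analysis: logistic regression with arm, RACE score as the stratification factor, and named pre-randomisation prognostic covariates such as age, pre-stroke mRS and time from onset. Report a standardised risk difference with its confidence interval, which keeps the scale of the stated primary outcome. Give the unadjusted difference in proportions as a sensitivity analysis. Baseline tables can stay descriptive.

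Limit covariates to values that describe the patient before randomisation. This excludes admission NIHSS.

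The cost is a few lines of wording and a slightly more complex primary analysis; the sample size does not change. RACE is recorded before hospital arrival in Table 2. Age, pre-stroke mRS and onset time must be known to establish eligibility, but Table 2 does not list the last two as separate recorded items, so confirm that their values, not only that the criterion was met, are captured. Make the change before any outcome data are seen by arm, since a model chosen later would not be credible.
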